### Outcomes {12}

The primary outcome is the proportion of participants who adhere to wearing their orthopedic shoes (see the “Proportion participants being adherent” section). We define adherence as minimally 80% of daily steps taken with orthopedic shoes based on the data of a randomized trial in The Netherlands [13, 14].

Secondary outcomes are 1) the level of adherence to wearing orthopedic shoes during 1 week at 3 and 6 months after inclusion; 2) the change in adherence between 3 and 6 months after inclusion; 3) total wearing time during 1 year follow-up; 4) the proportion of participants (re-)experiencing complications during 1 year follow-up; 5) the participant-perceived quality of life at inclusion and 3 and 6 months after inclusion; 6) the experiences of participants regarding their knowledge about the aim of orthopedic shoes, their satisfaction with communication with the pedorthist regarding wearing orthopedic shoes, their behavioral intentions, and their satisfaction with orthopedic shoes, at inclusion and 6 month after inclusion; 7) the experiences of podiatrists regarding their knowledge about motivational interviewing and their experiences and attitudes toward applying motivational interviewing in this group of patients, after all participants are included; 8) the application of motivational interviewing; and 9) foot care-related costs during 1 year follow-up. For an overview of all time points, see Table 2 (see the “Participant timeline {13}” section).

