**Table 2 Tab2:**
[figure not shown]
Overview of the measurements of the study parameters during the study

*Abbreviations*: *EQ-5D-5L* 5-Level EuroQol Quality of Life Scale, *iMCQ* iMTA Medical Consumption Questionnaire, *iPCQ* iMTA Productivity Cost Questionnaire, *m* months, *MOS* Monitor Orthopedic Shoes post-part, *RAND-36 V2.0* Research and Development 36-item Health Survey version 2.0, *wk* weeks

^1^The participants, who will not be approached for the in-depth interview, will be asked to fill in MOS

^2^The iPCQ will also be taken from participants after (re-) experiencing complications; taken 4 weeks after the complication was diagnosed

^3^Activity registration during 1 week

[37] [38] [40] [42] [44] and [47]

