#### Complications

The proportion of participants (re-)experiencing complications (i.e., one or more ulcers or abundant callus that requires debridement, not present at baseline, or lower-extremity amputation) will be determined by the registration of (re-)experienced complications after receiving their orthopedic shoes, up to 1 year after baseline. All complications will be registered and photographed by podiatrists, who are informed by the participant if complications occur (in > 95% of complications cases, the podiatrist is the first to hear from the participants). If it is necessary to obtain details on specific complications, general practitioners or orthopedic surgeons will be contacted. Photographs will be assessed by observers blinded to treatment allocation to confirm the type and/or severity of the complication.

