#### Foot care-related costs

Healthcare resource use of participants will be determined using the Institute for Medical Technology Assessment (iMTA) Medical Consumption Questionnaire (iMCQ) [42]. Cost prices will be calculated according to the 2015 Dutch guideline for health economic evaluation [43]. If relevant, costs of medication use will be derived from the Dutch formulary increased with a pharmacist’s charge. Costs of diagnostic tests will be based on Dutch tariffs, and, if applicable, costs of over-the-counter medication and alternative medicines will be based on average retail prices. Costs of consulting a general practitioner or medical specialist or other procedures and hospitalizations will be based on the 2015 Dutch guideline for health economic evaluation [31] or charges if no other estimates are available. The potential productivity losses from complications of the foot or the orthopedic shoes will be assessed using the iMTA Productivity Cost Questionnaire (iPCQ) [44] instrument among all participants at baseline and 12 months after baseline, and additionally among participants who present with complications, at 4 weeks after the complication was diagnosed [32]. A friction cost approach will be applied to estimate the productivity losses as defined in the Dutch costing manual and based on the reference costs of not being able to perform paid or unpaid work.

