In addition, a few small changes to the number of study consultations have also been made: 1) We reduced the number of six consultations that the participants would have with one of the investigators by two consultations. The investigator sees the participant at the delivery of the orthopedic shoes (T0), and 3 months (T1), 6 months (T2), 9 months (T3), and 12 months (T4) after the participant received their orthopedic shoes. 2) As a result of this change, the participants will receive the activity monitor during T1 (3 months) and T2 (6 months) instead of T1 (2 to 4 weeks) and T3 (4 months) as shown in Table 2. 3) All participants will be asked to fill in the MOS 6 months after receiving their orthopedic shoes, also the participants who will be approached for a second in-depth interview. 4) During every consultation with one of the investigators, the participant will be asked if they have an ulcer or have had an ulcer in the last 3 months. If so, the participant will be asked to fill in the iPCQ.

In conclusion, this trial aims to assess the (cost-)effectiveness of this novel care approach compared to usual care in terms of adherence to orthopedic shoes and ulcer prevention. The outcomes of this trial will generate insights into the socio-economic impact of the novel care approach on adherence to orthopedic shoes. These are crucial steps toward better ulcer prevention in high-risk diabetes patients.

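### The event-related productivity questionnaire is now triggered by ulcers only, at 3-monthly visits, so work loss from other complications may be seen only at 12 months

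*Protocol article*

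**What the plan says.** The section Foot care-related costs sets the purpose: "The potential productivity losses from complications of the foot or the orthopedic shoes will be assessed". Every participant completes the iPCQ at baseline and at 12 months. A further form is due "additionally among participants who present with complications, at 4 weeks after the complication was diagnosed". Footnote 2 of Table 2 agrees that the extra form is "taken 4 weeks after the complication was diagnosed".

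The Complications section defines the event as "one or more ulcers or abundant callus that requires debridement, not present at baseline, or lower-extremity amputation". Under Outcomes {12} the cost outcome is "foot care-related costs during 1 year follow-up", and the trial-based cost-effectiveness analysis has a one-year horizon.

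The Discussion then lists changes made after inclusion began. Investigator visits are now at delivery of the shoes and at 3, 6, 9 and 12 months. By change 4, at each of these visits "the participant will be asked if they have an ulcer or have had an ulcer in the last 3 months". It continues: "If so, the participant will be asked to fill in the iPCQ". Callus and amputation are not mentioned, and nothing is said about the form due 4 weeks after a complication.

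The Participant timeline {13} still has the investigator ask about complications in general at every study consultation. Health-care use is collected separately with the iMCQ. No section states the look-back period of the iPCQ.

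**The concern.** Change 4 alters two things. The trigger narrows from any complication to an ulcer. The timing moves from a fixed 4 weeks after diagnosis to the next scheduled visit, which may come anywhere from 0 to about 13 weeks later. The quantity to be costed has not moved with it: it is still productivity loss from complications over the full year.

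If the forms see only part of that loss in both arms, any productivity saving from preventing complications shrinks in proportion. That works against whichever arm prevents more of them, in a trial whose aims include cost-effectiveness and ulcer prevention. Because the change came during recruitment, early and late participants may also have had losses recorded over different windows.

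**Working it through.** The protocol gives no figure for work loss, episode length or look-back, so there is nothing to reproduce. The check is how much lost work time falls inside a window that some form can see.

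**Inputs from the protocol.** Forms after a reported ulcer at weeks 13, 26, 39 and 52 (Discussion); a form for everyone at 12 months, and a form 4 weeks after a complication (Foot care-related costs); a one-year costing period.

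**Assumptions.** Onset is uniform over 52 weeks. Work loss lasts D weeks from diagnosis and is cut off at week 52. Each form sees the R weeks before it. R and D are not in the documents, so ranges are shown.

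**Simple coverage.** Four forms a year cover 4R/52 = R/13 of the time:
- R = 2: 15%
- R = 4: 31%
- R = 8: 62%
- R = 13: 100%

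The 12-month form alone covers R/52: 4/52 = 8% at R = 4 and 13/52 = 25% at R = 13.

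**One ulcer case by hand.** Let D = 4, R = 4, with the visit uniform over the 13 weeks after diagnosis. The overlap of loss and window rises from 0 to 4 weeks and falls back to 0 at week 8, an area of 16. Mean capture is 16/13 = 1.23 of 4 weeks, or 31%. If the visit comes after week 8, nothing is seen: 5/13 = 38% of episodes.

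**Share of lost time seen, with episode length taken into account:**

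| R (weeks) | D (weeks) | 4-week form plus 12-month form | Ulcer, 3-monthly forms | Non-ulcer, 12-month form only |
|---|---|---|---|---|
| 4 | 4 | 100% | 32% | 8% |
| 4 | 8 | 56% | 33% | 8% |
| 4 | 13 | 40% | 34% | 9% |
| 4 | 20 | 31% | 34% | 10% |
| 4 | 26 | 28% | 34% | 10% |
| 8 | 4 | 100% | 64% | 16% |
| 8 | 13 | 46% | 65% | 18% |
| 13 | 4 | 100% | 100% | 26% |
| 13 | 13 | 54% | 100% | 29% |
| 13 | 26 | 48% | 100% | 33% |

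*Ulcers.* At a 4-week look-back the four-week rule sees more for losses up to about 16 or 17 weeks (35.2% against 33.5% at 16 weeks) and slightly less beyond that (33.1% against 33.6% at 18 weeks). At 13 weeks the visit rule sees everything, while the four-week rule falls to 48% for long episodes.

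*Non-ulcer complications.* If change 4 replaces the four-week form, only the last column applies. Over D from 1 to 26 weeks it gives 8–10% at R = 4 and 25–33% at R = 13. Even the longest look-back considered misses 67–75%.

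**Effect on the cost difference.** If a share s of the loss is recorded in both arms, the recorded productivity saving is s times the true one.

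**The case against.** The strongest reply is that no undercount has been shown for ulcers. With an unstated look-back, the missed share runs from 85% (2 weeks) through 69% (4 weeks) to 0% (13 weeks). The visit question itself spans three months, which matches the visit gap. The four-week rule also missed loss after week 4 of a long episode, so the change may improve capture. Multiplying each response by 13/R would remove the average bias if visit timing is unrelated to onset, and an analysis plan could properly settle that. All of this stands. A reader might infer that about 69% of ulcer-related work loss is lost; the documents do not support that as a finding.

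A reader might also call the sections contradictory. The Discussion announces change 4 as a change, and a declared change that differs from text it supersedes is not in itself an error. Nor does change 4 say that the four-week form is withdrawn: change 2 says what it replaces, change 4 does not. If the four-week form survives, non-ulcer complications keep their form.

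Other limits also stand. Health-care costs and the primary outcome are untouched, everyone completes the iPCQ at 12 months, and podiatrists register all complications. The protocol does not show that callus debridement causes much lost work, or that amputation without an ulcer in the preceding 3 months is common.

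The objection does not remove the non-ulcer gap. Read as a replacement, which is the natural reading of a listed change, change 4 no longer measures all that the costs section sets out to cost. Scaling ulcer responses cannot help, because these participants complete no form at the interim visits. Scaling the 12-month form would mean multiplying by 52/13 = 4 or 52/4 = 13 and assuming that its last weeks stand for the year.

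**Conclusion.** The point holds in a limited, conditional form. The trigger in change 4 is narrower than the protocol's own definition of a complication, and the fate of the four-week form is left open. If that form is dropped, work loss from non-ulcer complications is seen only by the 12-month iPCQ: about 8–10% at a 4-week look-back and 25–33% at 13 weeks. For ulcers the share seen is about R/13 and may be complete.

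The productivity part of the one-year costs may therefore be undercounted in both arms, which would shrink any productivity saving from prevented complications. How far this moves the ICER cannot be determined from the documents. A difference between arms, from participants being handled under different rules, is a possibility only, because the change is not dated. The figures rest on uniform onset, loss starting at diagnosis, and the assumed ranges of look-back and episode length. The point still merits action, because work loss that is not asked about cannot be recovered at analysis.

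**What to change.** - Reconcile Foot care-related costs, footnote 2 of Table 2, the Participant timeline and change 4 in the Discussion, so that one rule says when and for whom the event-related iPCQ is given.
- At each existing 3-monthly visit, trigger it on every complication in the Complications section since the previous visit, not only ulcers. The investigator is already meant to ask about complications then.
- Record work days lost since the previous visit, so that the window covers the whole interval being costed.
- State whether the form 4 weeks after diagnosis is kept. If it is, say how the two records are combined so that losses are not counted twice.

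This costs one or two extra questions at visits already planned and an amendment note, with no added visits or participants. The drawback is a longer recall period, with some loss of accuracy.

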## Trial status

The first version of this study protocol (22 January 2019) was registered at The Netherlands Trial Register (registration number NL7710, https://www.trialregister.nl/trial/7710) on 6 May 2019. The trial commenced recruitment in July 2019. Inclusion is currently ongoing and expected to be completed in December 2020.

## Abbreviations

AVG: Algemene verordening gegevensbescherming
BMI: Body mass index
BMS Lab: Behavioural management and social sciences lab
CEA: Cost-effectiveness analysis
CMO: Commissie mensgebonden onderzoek
COVID: Coronavirus disease
DANS: Data archiving and network services
EQ-5D-5L: 5-Level euroqol quality of life scale
EU: European union
GLMM: Generalized linear mixed model
ICER: Incremental cost-effectiveness ratio
iMCQ: iMTA medical consumption questionnaire
iMTA: Institute for medical technology assessment
iPCQ: iMTA productivity cost questionnaire
IWGDF: International working group on the diabetic foot
LISA: Library, ICT Services & archive
LOPS: Loss of protective sensation
MI: Motivational interviewing
MINT: Motivational interviewing network of trainers
MITI: Motivational interviewing treatment integrity
MOS: Monitor orthopedic shoes
PAD: Peripheral artery disease
QALY: Quality-adjusted life year
RAND-36: Research and development 36-item health survey
SPIRIT: Standard protocol items: recommendations for interventional trials
TIIM: The incredible intervention machine
UAVG: Uitvoeringswet AVG
USA: United States of America
WMO: Medical research involving human subjects act; in dutch: wet medisch-wetenschappelijk onderzoek met mensen
